# Effectiveness of interactive augmented reality-based telerehabilitation in patients with adhesive capsulitis: protocol for a multi-center randomized controlled trial

**DOI:** 10.1186/s12891-021-04261-1

**Published:** 2021-04-26

**Keywords:** Adhesive capsulitis, Telerehabilitation, Multi-center randomized controlled trial, Augmented reality

## Abstract

**Background:**

As the primary treatment for adhesive capsulitis, intensive and accurate home exercise is as important as physical therapy in hospitals. Augmented reality (AR)-based telerehabilitation has been implemented recently in various musculoskeletal conditions to increase patient compliance and enable patients to exercise with the correct posture. The objective of this study is to present a protocol for investigating the additive effect of interactive AR-based telerehabilitation in comparison with the usual care for patients with adhesive capsulitis.

**Methods:**

This study presents the protocol of a prospective, multi-center, single-blinded, two-armed randomized controlled trial (RCT). One hundred patients with stage I or II adhesive capsulitis will be recruited at the physical medicine and rehabilitation clinic. Patients will be randomly divided into two groups with 1:1 allocation. The intervention group will receive 3 months of hospital-based physical therapy in conjunction with home-based telerehabilitation. The control group will receive 3 months of hospital-based physical therapy in conjunction with a home-based exercise described in a brochure provided by the hospital. The primary outcome will be the change in passive range of motion (ROM) of the affected shoulder joint from baseline to 12 weeks after baseline assessment. The secondary outcomes will be active ROM, pain measured with the numeric rating scale, shoulder pain and disability index, 36-Item Short Form Survey, EuroQoL-5D-5L, and Canadian Occupational Performance Measure.

**Discussion:**

This will be the first RCT study protocol to investigate the effect of telerehabilitation in patients with adhesive capsulitis. The result of this RCT will determine whether AR-based telerehabilitation is more effective than a brochure-based home exercise program and will provide evidence of the usefulness of “telerehabilitation” using hardware (IoT) and software (monitoring platform) technologies to develop “digital therapeutics” for the future.

**Trial registration:**

This trial was retrospectively registered at the Clinicaltrials.gov website on 20 March 2020, with the identifier NCT04316130.

**Supplementary Information:**

The online version contains supplementary material available at 10.1186/s12891-021-04261-1.

## Background

Adhesive capsulitis, also known as “frozen shoulder,” is a common shoulder disease that clinically presents with pain, stiffness, and dysfunction and is pathologically characterized by inflammation and contracture of the glenohumeral capsule [1]. Although there are differences in the literature, adhesive capsulitis has a high prevalence rate of 2–5% in the general population, with the highest prevalence observed among women between 40 and 60 years of age [2]. Adhesive capsulitis consists of the first “freezing (painful)” stage with increased pain and stiffness for several months, a second “frozen (stiff)” stage resulting in loss of range of motion (ROM) of the shoulder, and a third “thawing (recovery)” stage, in which pain and ROM recover [3].

Adhesive capsulitis is generally described as a self-limiting disorder that without supervised treatment, often recovers within 2–3 years [4]; however, its natural history is not fully known, and recent studies have shown that it may result in long-term disability [1, 4–7]. One systematic review showed that appropriate interventions were essential in reducing long-term disabilities [8]. Rehabilitation including joint mobilization and therapeutic exercise is one of the most important interventions required for adhesive capsulitis [9]. Home exercise programs are as essential as physical therapy in hospital because of cost effectiveness and limited medical resources. Tanaka et al. [10] showed that better compliance with a home exercise program resulted in more improvement in adhesive capsulitis. However, home exercise programs are not easily quantified, and it takes time for doctors to explain and modify postures for each patient. Moreover, the accuracy and frequency of home-based rehabilitation may depend on the patient’s statement, rather than on objective and analyzed data. A key success factor of home-based programs is to increase adherence to the program, for instance through telerehabilitation.

Recently, research on telerehabilitation that uses telecommunication technology to provide rehabilitation services at a distance is increasing [11]. Recent systematic reviews have shown that telerehabilitation was comparable to the standard practice in improving physical function and reducing pain of musculoskeletal disorders, mainly for spine-related or postoperative conditions [12]. Developing and applying an AR-based telerehabilitation with specialized step-by-step exercises for patients with adhesive capsulitis is thought to increase clinical effectiveness and improve patient compliance.

We aim to present a protocol for investigating clinical effects of interactive augmented reality (AR)-based telerehabilitation in addition to hospital-based physical therapy through a randomized controlled trial (RCT) designed for patients with adhesive capsulitis. We hypothesize that interactive AR-based telerehabilitation in conjunction with hospital-based physical therapy would lead to better results than a brochure-based home exercise program with hospital-based physical therapy for 3 months post diagnosis.

## Methods/design

### Study design

This protocol will be a prospective multi-centered single-blinded two-armed RCT. The study design meets SPIRIT guidelines [13] and the SPIRIT Checklist are attached as Additional file 1. All eligible patients will be informed about this study and invited to participate by the outpatient doctor at the Physical Medicine and Rehabilitation clinic in Republic of Korea. All patients submit informed consent if they agree to participate in the study and principal investigator obtained the informed consent. After randomly divided into two groups with a 1:1 allocation, participants will be assessed in baseline. The intervention group will receive at least 3 months of hospital-based physical therapy in conjunction with home-based telerehabilitation. The control group will receive at least 3 months of hospital-based physical therapy in conjunction with a home-based exercise brochure provided by the hospital. The adhesive capsulitis stage will be evaluated at each follow-up by a physician, and exercises according to the stage will be prescribed. Outcomes will be assessed at the baseline and 1-month, 2-month, 3-month, 4.5-month, and 6-month follow-ups. Deviation of 7–15 days from each evaluation point will be allowed. Outcome measures will be performed by the same assessors, who will be blinded to the group allocation. The flow diagram of the study protocol is shown in Figs. 1 and 2.

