### Participants

In the protocol, we will enroll 100 participants with stage I or stage II adhesive capsulitis. The inclusion criteria will be as follows:
Age 19 years or aboveAffected shoulder joint restriction of at least 30° over the contralateral side for two or more of either forward flexion, abduction, or external rotation (with 90° shoulder abduction) when measured by a goniometer in the supine position [13].Able to receive in-hospital physical therapyAble to install telerehabilitation equipment at home

The exclusion criteria will be as follows:
Diagnosis of bilateral adhesive capsulitis [14]Secondary adhesive capsulitis caused by trauma (shoulder fracture, dislocation) and/or systemic inflammatory disease (rheumatoid arthritis) [13, 14]Unable to perform exercise due to general deconditioningCommunication difficulties

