### Randomization, allocation, and blinding

To randomly assign intervention, one researcher will generate a size 4 block randomization list through a computer-generated sequence. To conceal the random allocation, numbered, sealed, and opaque envelopes containing simple explanatory notes will be used to allocate treatment. Independent researcher will allocate the participants using computer-generated sequences with block size of four. The research member involving in randomization process will not participate in the enrollment and assessment process. Participants will be instructed not to tell the assessor which group they are randomized to during exercise and follow-up measurements.

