### Primary outcomes

The primary objective of this protocol is to determine the additive effect of interactive AR-based telerehabilitation in conjunction with hospital-based physical therapy on passive range of motion (PROM) for patients with adhesive capsulitis 3 months post diagnosis. Therefore, the primary outcome will be the change in PROM of the affected shoulder joint from baseline to 12 weeks after baseline assessment.

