### Statistical analysis

Subject demographics will be calculated using descriptive statistics. Kolmogorov–Smirnov test will be performed to assess the distribution of data. To compare baselines between the two groups, an independent t-test and chi-square test will be conducted. To compare the mean difference, if primary outcome (PROM) data in both groups is found to be normally distributed, we will perform an independent t-test, not Mann-Whitney test. How to handle missing data will be applied depending on distribution of data after study completed.

To investigate the effects of the interventions and differences between groups for secondary outcomes, a mixed effects model or generalized estimating equations will be conducted, with one between-subject factor (group: intervention and control) and one within-subject factor (evaluation time: baseline, 4-week, 8-week, 12-week, 18-weeks, and 24-week follow-ups). All data will be analyzed using IBM SPSS Statistics version 20.0 (Armonk, New York, USA) and a significance level of 5% will be set with a 95% confidence interval.

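### Baseline is assessed after randomisation, and nothing in the protocol keeps the arm from participants until the baseline of the change-score primary outcome is recorded

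*Protocol article*

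**What the plan says.** In the protocol article, the Study design section gives the sequence after consent: "After randomly divided into two groups with a 1:1 allocation, participants will be assessed in baseline". The Primary outcomes section then builds on that measurement: "the primary outcome will be the change in PROM of the affected shoulder joint from baseline to 12 weeks after baseline assessment".

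On blinding, the Study design section calls the trial single-blind ("This protocol will be a prospective multi-centered single-blinded two-armed RCT") and names the assessors as the blinded party: "Outcome measures will be performed by the same assessors, who will be blinded to the group allocation". One arm has a motion-capture system installed at home (Telerehabilitation section). The other receives a brochure and a log book (Brochure section).

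The section on randomization, allocation, and blinding describes the mechanism: "numbered, sealed, and opaque envelopes containing simple explanatory notes will be used to allocate treatment". It does not say when an envelope is opened relative to the baseline assessment. The same section gives the only non-disclosure rule: "Participants will be instructed not to tell the assessor which group they are randomized to during exercise and follow-up measurements". Baseline is not named there.

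The primary comparison is a two-group test: "if primary outcome (PROM) data in both groups is found to be normally distributed, we will perform an independent t-test, not Mann-Whitney test".

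**The concern.** Randomisation makes the arms comparable on anything measured before the allocation can act on the participant. A baseline taken afterwards has that protection only if the participant and the assessor do not yet know the arm. The protocol states the order that removes the protection and does not state the concealment that would restore it.

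There are two routes to harm:

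- **A shifted starting value.** Participants have stage I or II disease, and the Background section describes stage I as painful. Tolerance and guarding can influence where a passive movement stops. The pain, disability, quality-of-life and occupational-performance scores are the participant's own report and are more exposed. A participant who knows the arm could also reveal it at baseline, since the instruction not to do so does not name that visit.
- **A missing starting value.** Someone who leaves between randomisation and baseline has no change score and drops out of the primary comparison, possibly for reasons linked to the arm. The documents state no interval between the two events. If both fall within one visit, there is little time for this to happen.

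**Working it through.** **1. Is the order contradicted elsewhere?** The Study design section puts randomisation first. The sections on randomization, outcomes and statistical analysis say nothing that places baseline before allocation or before disclosure. Fig. 1, Fig. 2 and Table 1 could not be read in the text, so they neither confirm nor contradict the order.

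**2. The plan's own figures.** Inputs from the Sample size calculation section: SD of change 18.64, 16.79, 11.22 and 11.65 degrees; planned differences 15, 15, 10 and 10 degrees for flexion, abduction, external and internal rotation; alpha 0.05/4 = 0.0125 per direction, taken as two-sided; power 80%.

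n per group = 2 (z₀.₉₉₃₇₅ + z₀.₈₀)² (SD/difference)² = 2 (2.498 + 0.842)² (SD/difference)²

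- Flexion: 22.30 × (18.64/15)² = 34.4, so 35
- Abduction 28, external rotation 29, internal rotation 31
- The largest is 35. Allowing for 25% dropout, 35/0.75 = 46.7, so 47

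Both stated figures reproduce, so this point changes no figure in the plan.

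**3. How a shift enters the estimate.** Let b be the between-arm difference (intervention minus control) that knowledge of the arm causes at baseline, and p the fraction of it still present at 12 weeks.

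Bias in the difference in change = p·b − b = −(1 − p)·b

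- p = 0 (gone by 12 weeks): the bias equals the full shift in size
- p = 0.5: half the shift
- p = 1 (fully persistent): no bias from this route

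The sign follows b and is not known. For example, extra guarding in the brochure arm at baseline only would lower that arm's starting value, enlarge its change and understate the benefit of telerehabilitation. The same behaviour in the other arm would overstate it.

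**4. Illustration over an assumed range.** The documents give neither b nor p. The table takes net shifts (1 − p)·|b| of 1 to 5 degrees as an assumption, with 35 per arm, two-sided 0.0125 and a normal approximation. The standard error is SD × √(2/35): 4.46 degrees for flexion and 2.68 for external rotation. Without a shift, power is 0.807 for flexion and 0.891 for external rotation.

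| Net shift (degrees) | Share of 15 / of 10 | Null rejection, flexion | Null rejection, ext. rotation | Power if shift opposes effect, flexion | Same, ext. rotation |
|---|---|---|---|---|---|
| 1 | 7% / 10% | 0.0147 | 0.0188 | 0.740 | 0.805 |
| 2 | 13% / 20% | 0.0218 | 0.0405 | 0.663 | 0.686 |
| 3 | 20% / 30% | 0.0348 | 0.0841 | 0.577 | 0.545 |
| 5 | 33% / 50% | 0.0846 | 0.2632 | 0.400 | 0.263 |

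Example, 3 degrees, flexion: 3/4.46 = 0.673; the upper tail beyond 2.498 − 0.673 = 1.824 is 0.034; adding the lower tail of 0.001 gives 0.035.

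The table shows how sensitive the test is to a net shift. It does not estimate what will happen.

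**The case against.** The strongest reply is that the protocol never says participants know their arm at baseline. The envelope may stay sealed until the measurement is done. A non-disclosure rule that omits baseline also fits a trial in which there is nothing to disclose at that point. This stands: a reader might infer that every baseline is taken from a participant who knows the allocation, but the documents support only the order and the absence of a stated safeguard.

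Second, the primary outcome is fairly robust. It is passive motion, measured supine with an electronic goniometer by blinded assessors. Voluntary effort matters mainly for active motion, which is secondary, as are all the self-reported scales. This lowers the risk for the primary outcome but does not remove it, because pain and guarding can still limit a passive end range.

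Third, a reader might infer that any baseline shift passes in full into the treatment effect. As shown above, that needs the shift to have gone by 12 weeks.

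Fourth, a reader might worry that baseline adjustment would condition on a variable affected by allocation. The protocol plans no such adjustment: the primary test is a t-test or Mann-Whitney test, and the secondary models treat baseline as a level of the time factor.

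**Conclusion.** The point holds as a gap in the stated procedure. The protocol places baseline after randomisation in a trial whose participants cannot be blinded, and it states no concealment of the arm until baseline is recorded. Whether bias follows depends on three things that the documents do not settle: that the arm is known at baseline, that this knowledge shifts the measurement differently in the two arms, and that the shift has faded by 12 weeks. If all three hold, the difference in change is biased by the net shift, in an unknown direction. No single size can be defended, and the 1 to 5 degree range is an assumption.

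The concern is moderate for PROM and greater for the self-reported secondary outcomes. It does not invalidate the sample size or show that the trial is biased. It is worth correcting because the correction is cheap and the timing of a baseline cannot be changed once it has been taken.

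**What to change.** **Remaining participants.** Complete consent, eligibility and the full baseline assessment (passive and active motion and all questionnaires) before the envelope is opened. If the order cannot be changed, state that the arm stays undisclosed to participant and assessor until baseline is recorded. In either case, extend the non-disclosure instruction to the baseline visit. If this is already the practice, one clarifying sentence is enough.

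**Participants already enrolled.** Recruitment began in March 2020 and completion is expected in June 2022, so some baselines will already exist.

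- Report the actual order of baseline, randomisation and disclosure, and the number randomised without a baseline, by arm.
- Run a sensitivity analysis by order of baseline and randomisation.
- Use screening goniometry as an alternative baseline only with care. Eligibility rests on forward flexion, abduction and external rotation, "when measured by a goniometer in the supine position". Internal rotation is not required, so one of the four primary directions has no substitute. The article does not say that screening was passive, taken by a blinded assessor or made with the electronic device, so it can serve only if it was measured comparably.
- A comparison of 12-week PROM itself, without the baseline, would cover all four directions. Its precision cannot be judged from the documents.

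**Cost.** A short amendment and no added procedure. The downside is two baseline timings within one trial, which the analysis by order is meant to show.

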**Fig. 1 Fig1:**
[figure not shown]
RCT study flow chart

**Fig. 2 Fig2:**
[figure not shown]
Exercise intervention according to group allocation

### Participants

In the protocol, we will enroll 100 participants with stage I or stage II adhesive capsulitis. The inclusion criteria will be as follows:
Age 19 years or aboveAffected shoulder joint restriction of at least 30° over the contralateral side for two or more of either forward flexion, abduction, or external rotation (with 90° shoulder abduction) when measured by a goniometer in the supine position [13].Able to receive in-hospital physical therapyAble to install telerehabilitation equipment at home

The exclusion criteria will be as follows:
Diagnosis of bilateral adhesive capsulitis [14]Secondary adhesive capsulitis caused by trauma (shoulder fracture, dislocation) and/or systemic inflammatory disease (rheumatoid arthritis) [13, 14]Unable to perform exercise due to general deconditioningCommunication difficulties

### Randomization, allocation, and blinding

To randomly assign intervention, one researcher will generate a size 4 block randomization list through a computer-generated sequence. To conceal the random allocation, numbered, sealed, and opaque envelopes containing simple explanatory notes will be used to allocate treatment. Independent researcher will allocate the participants using computer-generated sequences with block size of four. The research member involving in randomization process will not participate in the enrollment and assessment process. Participants will be instructed not to tell the assessor which group they are randomized to during exercise and follow-up measurements.

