**Fig. 3 Fig3:**
[figure not shown]
UINCARE Home+ (left) and screen during exercise with real-time feedback (right) (A: guide video, B: holding time, exercise set and number)

The telerehabilitation protocol using the UINCARE Home+ is shown in Fig. 4. First, the physician will diagnose the patient’s stage of adhesive capsulitis and prescribe a corresponding exercise program. The UINCARE company device manager creates the user account and then, independent researchers set up the prescribed exercise program on the administrator page. The UINCARE Home+ will be delivered by the company, installed at the patient’s home, and the patient will be trained on how to use it. During the intervention period, independent researchers will monitor performance, accuracy, and check individual exercise schedules through the administrator page. Every month, the researcher will enquire of the related problem and encourage the patient to exercise at least once a day.

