### Ethics and dissemination

All study procedures were approved by the Institute Review Board of two hospitals (approval numbers: SMC-2019-05-021 and KC20ENDE0254). The trial was registered on clinical trials.gov (approval ID: NCT04316130). The study protocol was fires reviewed by the institutional review board of Samsung Medical Center on 17 May 2019 and was approved on 7 June 2019 as original protocol. If there are important protocol modifications, principal investigator will share them with coordinating investigators and trial participants, and report to institutional review board.

Personal information about enrolled participants will be collected, shared with clinic (i.e., Seoul St. Mary’s Hospital), and retained by only research team during study. After the end of the study, all personal information will be retained for 3 years and then destroyed.

The trial results will be published in the journal and report of results will be posted on the funding institute’s site for the public, participants, and healthcare professionals.

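### A fixed block size of four lets a recruiter who knows a block's earlier allocations foresee one third of assignments on average, or about 8 to 16% if only own-hospital allocations on a shared list are known

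*Protocol article*

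**What the plan says.** The section on randomization, allocation and blinding gives the block size twice. For the list, "one researcher will generate a size 4 block randomization list through a computer-generated sequence". For its use, "Independent researcher will allocate the participants using computer-generated sequences with block size of four". The abstract sets the ratio: "Patients will be randomly divided into two groups with 1:1 allocation". Nothing indicates that sizes vary or that the size is withheld from recruiting staff.

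Concealment relies on envelopes: "numbered, sealed, and opaque envelopes containing simple explanatory notes will be used to allocate treatment". The same section bars whoever handles randomization from enrolling or assessing patients.

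The roles named as blinded are the outcome assessors (Study design, Outcomes) and the hospital therapists (Interventions). Patients are told to keep their group from the assessor, so they know it themselves.

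On the recruiting side, Study design says patients are "invited to participate by the outpatient doctor at the Physical Medicine and Rehabilitation clinic", and the principal investigator takes consent. Telerehabilitation opens its workflow with a doctor's step: "the physician will diagnose the patient’s stage of adhesive capsulitis and prescribe a corresponding exercise program". The Discussion describes home exercise in that arm as remotely supervised by a physician.

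Two hospitals take part (Ethics and dissemination: "All study procedures were approved by the Institute Review Board of two hospitals"). The article does not say whether they share one list or have one each.

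**The concern.** With a constant 2:2 block of four, the fourth assignment always follows from the first three. The third also follows whenever the first two went to the same arm. An opaque envelope hides its contents from inspection but not from this reasoning. Home equipment and a paper brochure are hard to confuse once a patient returns to the clinic, so earlier allocations can plausibly become known there.

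Selection at enrolment is at stake. Some eligibility criteria leave room for judgement (deconditioning, communication difficulties), and the time of invitation is in the doctor's hands. A recruiter who foresees the arm could favour or defer a patient, even without intending to. The Background links better compliance with home exercise to more improvement, so choosing patients by expected motivation could carry through to passive range of motion.

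**Working it through.** **Inputs.** Block size 4 and the envelopes (Randomization, allocation, and blinding); ratio 1:1 (abstract); 100 patients, so 25 blocks (Participants); two hospitals (Ethics and dissemination); recruitment from 4 March 2020, completion expected June 2022 (Trial status); publication 26 April 2021.

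**The plan's own figure.** The article states no predictability figure. Its sample size reproduces and is not affected by this point: for flexion, 2 × (2.498 + 0.842)² × (18.64/15)² = 34.4, so 35 per group, and 35/0.75 = 46.7, so 47.

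**Step 1. Certain assignments when all earlier allocations in the block are known.** There are six balanced blocks.

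| Block | Certain positions | Count |
|---|---|---|
| AABB, BBAA | 3 and 4 | 2 each |
| ABAB, ABBA, BAAB, BABA | 4 | 1 each |

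Share certain = (2 × 2 + 4 × 1)/(6 × 4) = 8/24 = 33.3%. A single block ranges from 25% to 50%. Over 25 blocks the expectation is 25 × 4/3 = 33.3 of 100 patients, with a simulated 95% range of about 29 to 38. One third is therefore a mean and not a ceiling.

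**Step 2. Best guessing in the same setting** (guess the arm with more places left; toss a coin if equal).
- Position 1: 1/2
- Position 2: 2/3
- Position 3: (1/3) × 1 + (2/3) × 1/2 = 2/3
- Position 4: 1

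Mean = (1/2 + 2/3 + 2/3 + 1)/4 = 70.8%, against 50% with no information.

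**Step 3. One list shared by both hospitals, own-hospital allocations only.** Let p be the hospital's share of patients, and assume the numbered envelopes reveal the position in the block. Position 3 is certain if both earlier patients were at this hospital and in the same arm: p² × 1/3. Among the first three places two always share an arm, so position 4 is certain if both of those patients were at this hospital: p². Positions 1 and 2 are never certain.

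Share certain = (p²/3 + p²)/4 = p²/3.
- p = 0.5: 0.25/3 = 8.3%
- p = 0.7: 0.49/3 = 16.3% (the 30% hospital would have 0.09/3 = 3%)

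Simulation agrees (8.3% and 16.4%). Best-guess success is then about 60% and 64%.

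**Step 4. The alternative.** I compared larger fixed blocks (enumerated) with randomly mixed blocks (1,000 simulated trials of 100 patients, sizes equally likely). In the mixed case the guesser knows every earlier allocation and the set of sizes, but not their order.

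| Scheme | Certain | Best guess correct |
|---|---|---|
| Fixed 4 | 33.3% | 70.8% |
| Fixed 6 | 25.0% | 68.3% |
| Fixed 8 | 20.0% | 66.6% |
| Mixed 4 and 6 | 5.6% | 69.2% |
| Mixed 4, 6 and 8 | 2.3% | 67.9% |

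A larger fixed block helps little. Hidden variation in size removes most of the certainty, while the guessing rate hardly moves.

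**The case against.** Several points on the other side are sound.

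- **Doctors' knowledge is inferred.** A reader might take it as stated that recruiting doctors learn allocations. No sentence says so. The prescription follows disease stage, the exercise programme is the same in both arms, and independent researchers set up and monitor the device. The inviting doctor need not be the prescribing one. Still, neither is named as blinded, patients know their group, and the Discussion has a physician supervising the device arm. The inference is reasonable and is labelled as one.
- **The one-third figure is conditional.** It needs a list per hospital or knowledge shared between hospitals. On a shared list with own-hospital knowledge the range of about 8 to 16% applies.
- **Publication adds only a little.** It can inform only enrolments after 26 April 2021, and their number is not given.
- **The safeguards are real.** Separating the allocator from enrolment protects the list, and every participant in either arm must be able to install the equipment, which narrows one route to selection. Neither stops deduction from allocations already known.

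Two further readings are tempting but not supported. One is that randomization is not stratified by hospital. The article is silent on this, and a condensed article may leave it to the full protocol. The other is that hospital should enter the primary analysis as a covariate. That would not reduce predictability, and the planned comparison is an independent t-test or a Mann-Whitney test, which has no covariates.

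**Conclusion.** The point holds as a conditional design weakness. The fixed size of four is stated outright, and the arithmetic that follows is exact. The size of the problem depends on what recruiters know: 33.3% of assignments certain on average with full knowledge of the block, and about 8% (equal hospitals) to 16% (at a hospital with 70% of patients) with own-hospital knowledge of a shared list. It would be nil if recruiters never learned any allocation, which the article does not establish. All these figures also assume that recruiters know where each block starts.

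This shows an opportunity for selection, not a bias. Nothing in the article shows that selection has occurred, and no effect on range of motion can be estimated from it.

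**What to change.** For all participants not yet randomized, the independent researcher generates a new list with randomly varying block sizes, for example 4, 6 and 8, and issues new numbered, sealed envelopes. Sizes and order stay with that researcher and away from everyone who invites patients or takes consent.

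The change should go to the institutional review boards. Ethics and dissemination has the principal investigator report important modifications and share them with coordinating investigators and participants, and the principal investigator also takes consent. The general notice should therefore say only that the sequence has been replaced, with the sizes lodged separately and in confidence.

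The cost is one list, one set of envelopes and one notification. Final imbalance could be slightly larger. On one list, an abandoned block of four leaves a difference of at most 2 and an unfinished block of eight at most 4, so 6 in all. A 53:47 split of 100 raises the variance of the group difference by a factor of (1/53 + 1/47)/(2/50) = 1.004, which is negligible.

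If enrolment has already closed, the trial report should state the fixed block size, how the list was organised across hospitals, and who could know earlier allocations.
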